#### Randomization and data management

Owing to the limited number of samples in this research, census sampling method will be used by telephone invitation to all participants who meet the inclusion criteria. The names and phone numbers of the female survivors of sexual assault who were referred to the Social Emergency and Forensic Medicine of Isfahan City and who have files will be extracted from the archive and in coordination with the admission officer of the centers, and they will be invited to participate in the study. We will use the table of random numbers to randomly assign the participants to the two groups of intervention and control based on a one-to-one ratio. The participants’ recruitment will begin in April 2024, and will end in January 2025.

### Description of the intervention

#### Intervention group

In this research, by the intervention program based on social cognitive theory we mean the design and development of educational content based on this theory, using the opinion of experts in the field of clinical psychology, reading articles and psychology books, considering the nature of theoretical structures, and using different methods for the intervention group in order to focus on the individual's behavior in the areas of behavioral, environmental and individual factors. Social cognitive learning theory is concerned with the learning of patterns of behavior and the interaction between the individual and the environment. Thus, not only does the individual's response to the environment play a central role, but intellectual processes, i.e. cognitive operations resulting from human interaction with the environment and intrapersonal factors also play a fundamental role. The selected constructs in this research are awareness, self-efficacy, outcome expectations and environment, which will be used in the design of the intervention program focusing on health behavior change. In this study, environmental constructs and self-efficacy will be examined under the heading of perceived social support and perceived self-efficacy using standard questionnaires.

#### First phase: design and development of the program and content

In order to design the study and the content of the educational intervention based on the selected constructs of social cognitive theory, a search will be conducted in various sources of national and international articles using keywords such as sexual assault, education, social cognitive theory, sexual violence and post-traumatic stress disorder. In addition, psychology books and theories of midwifery, women and health will be examined.

An educational intervention will be carried out for the intervention group taking into account the nature of the theoretical constructs and using different methods to focus on individual behavior in the areas of behavioral, environmental and individual factors. The selected constructs in this study include awareness, self-efficacy, outcome expectations and environment, which will be used in the design of the intervention program focusing on health behavior change. Environmental constructs and self-efficacy will be examined under the titles of perceived social support and perceived self-efficacy using standard questionnaires. The intervention is designed for 40 participants, and for validation the opinions of expert professors and the research team will be used, and after their approval the intervention will be started. Education is delivered by the student and the research clinical psychologist using approved content during sessions.

#### Second phase: implementation of the intervention and training sessions

The instructor is a Master of Forensic Midwifery student and all training is delivered under the supervision and approval of the research team and the research team's clinical psychologist, and the content is approved by the research team. Participants in the intervention group will be taught about health, hygiene, psychology and stress reduction methods in group or individual sessions according to their preference in 6 sessions of 60 min each, one session per week. After obtaining the ethics permission from Isfahan University of Medical Sciences and the IRCT code, a letter of introduction is obtained to be submitted to Isfahan Welfare and Forensic Medicine Organizations. Written permission will be obtained from the officials to enter and access the medical files, and the researcher will be present in the research environment and introduced to the officials. The objectives of the research and the method of doing the study will be explained. An educational intervention is designed and developed, taking into account the constructs of social cognitive theory and focusing on health-related behavior. Sampling will take the form of a census of the participants who meet the eligibility criteria after accessing the file in the above-mentioned centers, and they will be invited to participate in the study by telephone. The participants are randomly assigned to the intervention and control groups using a random number table. Before participating in the research, they will be given a description of the research objectives, the intervention method and sufficient assurances of confidentiality, and they will be able to choose whether to participate in group or individual sessions to receive the educational intervention. Written consent will be obtained from the participants to participate in the research, and pre-test will be performed. Participants allocated to the intervention group will be invited to participate in four groups of 5 participants according to their age and education, or if they do not wish to be in a group, they will be invited to attend individual sessions. Then, an educational intervention based on social cognitive theory will be implemented in the Welfare and Forensic Medicine Organizations during 6 sessions of 45–60 min once a week and for 6 weeks by a trained instructor. The qualification of this instructor is confirmed by the consulting professor, [name], [PhD in clinical psychology] during a three-session program with health-related educational content. In order to provide the educational intervention [attached], the student will conduct the intervention based on social cognitive theory constructs in sessions under the supervision and approval of the team psychologist, and two sessions will be carried out in the presence of the professor. The educational content has been prepared on the basis of theoretical constructs and using the scientific techniques available in psychological articles and books, and taking into account the conditions required for the training, and will be analyzed and approved by the supervisor and advisor. In order to make the intervention in the direction of social support and environment, according to the specific social conditions, educational brochures will be given to the individuals to have the influence of the environment, so that they can request social support from the supportive people or give the brochure to their supporters and receive the education indirectly. It should be noted that in parallel with the intervention group, in order to double-blind the control group, a one-hour session for the control group will be provided with the routine training of the above-mentioned centers, without focusing on specific theoretical structures and continuous follow-up of sexually transmitted diseases. During the study, they will use the services and routine care provided by the centers, they will not be deprived of these services, and the researcher will not know about the groups. The time required for the research process [proposal preparation and approval, sampling and intervention, final report and article preparation, article editing and submission] is 14 months. Brochures, booklets and CDs with the same content as the sessions are used as teaching methods to make the sessions more accessible. For two months after the end of the intervention, the participants will be followed up, if necessary, through a telephone line, virtual group and SMS, and their questions will be answered. A post-test will be conducted for both groups to check the effect of the educational intervention two months after the last intervention session in the intervention group. This study is conducted to measure the effect of the independent variable (intervention training) on the dependent variables health-related awareness, health-related attitude and behavior, self-efficacy, perceived social support and PTSD severity score of women with experience of sexual assault. It also aims to reduce the symptoms of stress disorder, increase awareness, and improve health-related attitude and behavior, self-efficacy and perceived social support. The variables of background characteristics, self-efficacy, perceived social support, post-traumatic stress disorder, awareness and health-related attitudes and behaviors will be measured using a self-report questionnaire before and two months after the intervention in two groups. The measurement tools used in this research include a questionnaire on demographic characteristics, a standard questionnaire on self-efficacy, a standard questionnaire on perceived social support, PCL-5 post-traumatic stress disorder questionnaire, and a researcher-made questionnaire on health-related awareness, attitude and behavior. The questionnaire will be filled as self-report, and if a participant is illiterate, it is read out to them. It is hoped that by using the constructs of social cognitive theory in the content of training sessions based on scientific documents, it will be possible to meet the needs of these participants and prevent further injury and problems.

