### Study design

This study is randomized, double-blind clinical trial research that will be conducted on 40 women with experience of sexual assault referred to Iran-Isfahan Welfare and Forensic Medicine Centers. In the first phase of the educational intervention, the program, content and questionnaire will be designed and compiled, and in the second phase, sampling will be performed in the form of a census and, then, training sessions will be held. For the purpose of randomization, table of random numbers will be used for two intervention and control groups with a ratio of 1:1. The design of this clinical trial follows the requirements of the CONSORT statement.

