To measure the health-related awareness, attitudes and functioning, a researcher-made questionnaire was designed and developed using articles and psychology books. This questionnaire contains 21 items and includes 7 questions on awareness, 7 questions on attitudes and 7 questions on functioning in relation to health. To assess validity and reliability of the questionnaire, the final review will be conducted by 11 professors from Isfahan School of Nursing and Midwifery, Department of Health Psychology, Social and Forensic Medicine, and an epidemiologist. For example, a health-related awareness question is "There are drugs that can prevent the occurrence of sexually transmitted infections" that is scored 1 for a correct answer and 0 for an incorrect answer and I don't know. A health-related item of attitudes is "I am afraid to talk about sexual assault with my relatives", which is measured on a 5-point Likert scale. An example of a health-related behavior item is "To check for complications after rape, I do a genital examination", which is measured using a 4-point Likert scale. Data collection will be performed using a questionnaire on demographic characteristics, GSE-10 self-efficacy questionnaire, a questionnaire on perceived social support, PCL-5 post-traumatic stress disorder questionnaire, and a researcher-made questionnaire on health-related awareness, attitude and behavior. If the research samples did not have a correct understanding of the meaning of the word at the time of completing the questionnaire, it would be explained to them by the questioner.

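### The trial is labelled double-blind, but participants and instructors cannot be blind and the follow-up outcomes are self-reported

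*Protocol article*

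**What the plan says.** The protocol article uses the double-blind label in the Methods/design paragraph of the abstract and again under Study design: "This study is randomized, double-blind clinical trial research". The section on the second phase explains how this is to be achieved. It says that "in order to double-blind the control group, a one-hour session for the control group will be provided", consisting of the centres' routine training, and that "the researcher will not know about the groups".

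The same section describes what women experience. Before taking part they are told the aims and the intervention method, and they choose between group and individual sessions. The intervention is given "in 6 sessions of 60 min each, one session per week" (45 to 60 minutes further down the section), with printed and recorded materials that repeat the content. On delivery, it states that "the student will conduct the intervention based on social cognitive theory constructs in sessions". The First phase section adds the team's clinical psychologist as a second teacher.

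The Control group section gives controls routine care and continuing instruction on following up sexually transmitted infections. Under Data collection tools and methods, the researcher talks to each woman about her follow-up after she has been randomized. The outcomes are self-report questionnaires. They are read aloud to women who cannot read, and where a word is not understood, "it would be explained to them by the questioner".

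**The concern.** Double-blind tells a reader that neither the participant nor the person delivering or assessing treatment knows the arm. Here the statement conflicts with the article's own description of consent, delivery and measurement.

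This matters more than usual because of the outcomes. A woman who knows she received the programme may rate her symptoms, attitudes and behaviour differently for that reason alone. Items on disclosure to relatives or on seeking an examination have answers that the sessions may have taught as desirable. A reader who relies on the label would credit the results with a protection that they lack.

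**Working it through.** **Step 1. Set the blinding claim against each role.**

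| Role | What the article states | Can the role be blind? |
|---|---|---|
| Participant, intervention | Told the method, chose a format, attends six weekly sessions, keeps the materials | No |
| Participant, control | Told the method, then receives a one-hour routine session that is not theory-based, routine care and STI training | No: what she receives does not match what was described |
| Instructors (student, psychologist) | Teach the six sessions | No |
| The researcher | Said not to know the groups, but speaks to each woman about follow-up after randomization | Unclear: the person meant is not identified |
| Outcome assessor | The participant, by self-report | No, because the participant is not blind |
| Data handler or analyst | Not described | Possible, but would not protect self-reported answers |

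The control session would blind participants only if the two packages could not be told apart. Six sessions of 45 to 60 minutes come to 6 × 45 = 270 minutes to 6 × 60 = 360 minutes, that is 4.5 to 6 hours over six weeks. The added control session is 1 hour. The 1 hour is not the control arm's total contact, because the Control group section adds continuing STI instruction of unstated length. The packages still differ in number, content and materials.

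**Step 2. Reproduce the plan's own figure.** Inputs from Sample size: SDs 7.95 and 8.06, difference 7.5, α = 0.05 (two-sided assumed), power 80%.

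- Pooled SD = √[(7.95² + 8.06²)/2] = 8.005.
- n per arm = 2 × [8.005 × (1.960 + 0.842)/7.5]² = 17.88, rounded up to 18.
- With 10% dropout: 18/0.9 = 20.

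The stated 18 and 20 reproduce. The blinding problem does not alter the sample size.

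**Step 3. Illustrate what a bias could do.** The documents give no size for it, so a shift of 0.2 to 0.4 SD is assumed.

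- 0.2 × 8.0 = 1.6 points, and 1.6/7.5 = 21% of the target difference.
- 0.4 × 8.0 = 3.2 points, and 3.2/7.5 = 43%.
- Standard error at 18 per arm = 8.005 × √(2/18) = 2.668. The shift in standard-error units is 1.6/2.668 = 0.60 to 3.2/2.668 = 1.20.
- Two-sided t-test on 34 degrees of freedom with no true effect: rejection probability 9.0% at 1.6 points, 14.1% at 2.4 and 21.4% at 3.2, against a nominal 5%.

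The planned test is a repeated-measures analysis of variance, not this t-test. With two time points and equal SDs, its group-by-time test uses the variance of the change, 2 × SD² × (1 − r), where r is the pre-post correlation. This equals SD² only at r = 0.5. For a bias at post-test alone, a higher r gives higher rates and a lower r gives lower ones. The article does not give r.

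**The case against.** Participant blinding is rarely feasible for an educational programme, and an unblinded trial against usual care is legitimate. Both packages are described openly, so a careful reader can see what was done. Removing the label changes no estimand, test or sample size. All of this is fair, but it argues for describing the trial as unblinded, not for keeping the label.

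Several stronger readings are tempting, and the documents do not support them:

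- **Controls get only one hour of contact.** The Control group section adds routine care and STI instruction.
- **Only the intervention arm gets two months of telephone and message contact.** That contact is offered where needed, and the sentence names no arm.
- **Nobody on the team can be blind.** The term researcher is ambiguous, and a separate data handler or analyst could be masked.
- **The instructor will administer the questionnaires.** The article does not say so. An article may leave that detail to the full protocol, so its absence is not counted as an error here.
- **The registry entry is wrong.** The article gives only its number and dates.
- **Failure to separate theory content from contact time is a design flaw.** The stated aim is the effect of the training programme, which a usual-care comparator can address. The point is at most a limit on interpretation.
- **All outcomes are equally exposed.** The awareness items are scored right or wrong and leave less room for bias than the PCL-5, attitude or behaviour items.

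**Conclusion.** The double-blind statement is wrong as written for participants and for those who teach the sessions, and the claim about the researcher conflicts with the rest of the article unless the person meant is identified. This follows from the text alone and needs no numerical assumption.

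The consequence is that the self-reported follow-up results are open to bias from known allocation. The size of that bias is unknown. The 9% to 21% range depends on an assumed shift of 0.2 to 0.4 SD and on a t-test in place of the planned analysis, so it shows plausibility and is not an estimate. A reader might infer that the result will be biased by a known amount, or that the trial is invalid. Neither follows. What fails is a stated design property, and it is cheap to correct.

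**What to change.** 1. Remove the double-blind label from the abstract and Study design, and from the registry entry if it carries the same label. Describe the trial as unblinded for participants and instructors.
2. State which role, if any, is blinded. Reconcile the First phase, Second phase and Data collection sections on who the researcher is and what that person knows.
3. Have an existing team member who does not teach the sessions and has no access to the allocation list give, read out and explain both the pre-test and the post-test, using a fixed script. The pre-test is included because the Second phase section describes assignment before consent and pre-test. The Trial status section reports that 40 participants have already been selected. If any pre-tests have been done, report who gave them and apply the rule from then on.
4. Analyse with the arms coded A and B.
5. Report the self-reported results as open to bias from known allocation.

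The cost is revised wording, possibly a registry update, and some reassignment of questionnaire sessions within a small team. The risk-of-bias rating will be less favourable. Steps 3 and 4 limit the influence of staff but cannot blind the participant, so step 5 is needed in any case.

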
### Control group

The control group will continue to receive routine care, plus ongoing training on how to follow up sexually transmitted infections. The routine care that is done in our country is that, if a woman is sexually assaulted, she should first go to the police headquarters. Then the police introduce her to one of the court's branches that deals with rape issues. The judge introduces her to the Forensic Medicine, where the investigation of the raped woman is conducted, and the evidence and documents of the court case are presented, and according to the administrative procedures, they try to reach the rapist. At the same time, if the woman is raped, she will be introduced to a counselor who is present in the court so that she can be consulted and taken care of. Any type of health care (HIV test, prophylactic medication for STI, etc.) is done by raped women in private centers or comprehensive health service centers. Figure 1 details the flow of participants from enrollment until the last follow-up contact for control and intervention subjects.

**Fig. 1 Fig1:**
[figure not shown]
Flow diagram of the participants through the trial

### Sample size

According to the mean values and standard deviation before and after the educational intervention in previous studies [26] and asking the opinions of statistics experts and considering α = 0.05 and β = 0.2, the standard deviations of 7.95 and 8.06 in the intervention and control groups, and a minimum difference of 7.5 points between the two groups in terms of post-traumatic stress disorder, the sample size is calculated to be 18 participants in each group. However, considering a drop-out rate of 10%, the sample size is set at 20 participants in each group.

#### Data collection tools and methods

After the woman is randomized to the control or intervention group and has signed the written consent, having been previously informed of the study aims, the researcher will let her know about the follow-up she will need to complete during the study. The measurement tools used in this research include a questionnaire on demographic characteristics, GSE-10 self-efficacy questionnaire, a questionnaire on perceived social support, PCL-5 post-traumatic stress disorder questionnaire, and a researcher-made questionnaire on health-related awareness, attitude and behavior.

The Demographic Characteristics Questionnaire covers demographic information such as age, economic status, education level, occupation, marital status, number of children if married, spouse's education and occupation, residential status, birth order, parents' education and health insurance status. The number of supporters, number of rapes, previous experience of rape, relationship with the rapist, number of rapists and beatings during the event can be recorded using the researcher-made checklist. For example, "what is your birth order in your family?".

To examine perceived social support, the Multidimensional Perceived Social Support Scale is used, which measures social support from three sources of family, society and friends, using 12 items on a 7-point Likert scale ranging from “strongly disagree” (score 1) to “strongly agree” (score 7). The minimum and maximum scores for a person's perceived social support on the whole scale are 12 and 84, respectively, with the higher the score, the greater the social support. The validity and reliability of the tool has been checked and confirmed by Besha rat [27, 28]. A sample item is "There is a special person in my life who helps me when I need help", and is measured on a 7-point Likert scale.

Post-traumatic stress disorder in the present study refers to a score confirmed by the PLC-5 questionnaire and the opinion of a clinical psychologist. The PCL-5 is a self-report psychometric measure of PTSD symptoms according to the DSM-5, developed by Weds et al. [29]. The PCL-5 is a 20-item questionnaire, with a 5-point Likert scale (0–4) including 0( not at all), 1 (a little bit), 2 (moderately), 3 (quite a lot) and 4 (extremely) and the total score is calculated with a range of 0–80. Higher scores indicate a greater degree of severity of PTSD in the individual. The validity and reliability of the Persian version was assessed and confirmed by Vermaghani et al. in Iran. The optimal cut-off points for identifying possible positive cases of PTSD in the Iranian population are considered to be 33 [30]. The Cronbach's alpha of the English version of this instrument is 0.95 and the French version is 0.94. The validity and reliability of this instrument in Iran was assessed by Vermaghani et al., and the Cronbach's alpha coefficient for the Persian version was reported to be 0.92 [31, 32]. The questionnaire has been validated by the research team. An example of a checklist item is "extremely negative emotions such as fear, anger, guilt and shame", which is determined by a score of 0 to 4.

Self-efficacy in this research is the score that participants will receive on the General Self-Efficacy Scale (GSE-10). This questionnaire was developed and revised by Schwarzer and Jerusalem with the aim of assessing general self-efficacy [33, 34]. This questionnaire was implemented in Iran by Rajabi [35] on 587 students of Shahid Chamran University of Ahvaz and Marvdasht University. This scale has 10 items on a Likert scale from 1 to 4, with the lowest and highest scores being 10 and 40, respectively. The scale is used to predict adjustment after life transitions or as an index of how life is going at each stage of development, for clinical work and for behavior modification. The Cronbach's alpha coefficient of the GSE-10 scale in Iran is 0.84, which is higher than the standard in different countries, suggesting that it has a high reliability. A sample item of the scale is "If I try hard enough, I can always solve difficult problems", which is measured on a Likert scale of 1–4 ranging from "completely true" to "not true at all".

To measure the health-related awareness, attitudes and functioning, a researcher-made questionnaire was designed and developed using articles and psychology books. This questionnaire contains 21 items and includes 7 questions on awareness, 7 questions on attitudes and 7 questions on functioning in relation to health. To assess validity and reliability of the questionnaire, the final review will be conducted by 11 professors from Isfahan School of Nursing and Midwifery, Department of Health Psychology, Social and Forensic Medicine, and an epidemiologist. For example, a health-related awareness question is "There are drugs that can prevent the occurrence of sexually transmitted infections" that is scored 1 for a correct answer and 0 for an incorrect answer and I don't know. A health-related item of attitudes is "I am afraid to talk about sexual assault with my relatives", which is measured on a 5-point Likert scale. An example of a health-related behavior item is "To check for complications after rape, I do a genital examination", which is measured using a 4-point Likert scale. Data collection will be performed using a questionnaire on demographic characteristics, GSE-10 self-efficacy questionnaire, a questionnaire on perceived social support, PCL-5 post-traumatic stress disorder questionnaire, and a researcher-made questionnaire on health-related awareness, attitude and behavior. If the research samples did not have a correct understanding of the meaning of the word at the time of completing the questionnaire, it would be explained to them by the questioner.

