#### Inclusion criteria

Women aged 18–45 years.Women with at least one experience of sexual assault with an interval of at least one month from the incident [if there are symptoms of the disorder, no maximum], and obtained a score of 33 and above in PCL-5 questionnaire with the ability to diagnose based on the DSM-5 diagnostic system and the PTSD was confirmed in them by a clinical psychologist.No current drug use.No current major brain disease.No mental retardation.No major psychiatric disorder.No treatment process.No psychiatric history.No psychiatric record [psychotic disorders: psychosis, bipolar disorder, schizophrenia, bipolar I disorder with psychotic symptoms, dementia], and no pregnancy at study entry.

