### Trial status

This research was registered in Iran Clinical Trials Registration IRCT20230926059526N1 on 26 October 2023. To date, 40 participants have been randomly selected. It is expected that the recruitment of participants will be completed in March 2024.

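### The written order puts random assignment before consent and before the baseline PCL-5, so refusals and baseline scores could depend on the arm

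*Protocol article*

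**What the plan says.** The section on the second phase (implementation and training sessions) is a step-by-step account. After file access and telephone invitation it says: "The participants are randomly assigned to the intervention and control groups using a random number table". The study is then explained, and of the women it says that "they will be able to choose whether to participate in group or individual sessions to receive the educational intervention". Next comes: "Written consent will be obtained from the participants to participate in the research, and pre-test will be performed".

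Data collection tools and methods opens in the same order: "After the woman is randomized to the control or intervention group and has signed the written consent".

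Under Inclusion criteria, a woman must have "obtained a score of 33 and above in PCL-5 questionnaire", with PTSD confirmed by a clinical psychologist. Randomization and data management says that a "census sampling method will be used by telephone invitation to all participants who meet the inclusion criteria", so the women called are described as eligible already. The implementation section likewise speaks of women found eligible once the file has been accessed. It also says that the researcher is to be unaware of the groups.

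**The concern.** Randomisation makes two groups comparable at the moment of allocation. That comparability is protected only if what decides who is in the trial, and what is recorded as baseline, is settled before the arm can be known. In the written order, three things come after assignment: the woman's decision to take part, her choice of session format and her pre-test.

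This matters more here than in many trials. All outcomes, including the PCL-5, are self-reported. The intervention arm has six weekly sessions and the control arm a one-hour session of routine training, so the arms are easy to tell apart. Group or individual format is a choice that only the intervention arm can use, yet it is offered before consent. The article names a random number table and a 1:1 ratio, and describes no step that keeps the next assignment from those who recruit. With 20 women per arm, a few refusals linked to the arm could alter the comparison.

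**Working it through.** **1. The order, section by section.**

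| Step | Implementation section | Data collection section |
|---|---|---|
| Invitation by telephone | first | not mentioned |
| Random assignment | second | named first |
| Explanation and choice of format | third | informed of the aims at some earlier point |
| Written consent | fourth | named second |
| Pre-test (includes PCL-5) | fifth | measurements follow |

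The data collection sentence joins its two conditions with a plain conjunction and could be an unordered list. The implementation section gives the same order as a narrative. No section gives the reverse.

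**2. When the PCL-5 is taken.** It is both an entry criterion and an outcome. The only baseline administration described is the pre-test, which follows assignment. The article calls invited women eligible but describes no earlier step that yields the score.

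**3. The plan's own sample size.** Inputs from Sample size: SDs 7.95 and 8.06, difference 7.5, α = 0.05 (taken as two-sided), β = 0.2.

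n per arm = (1.960 + 0.842)² × (7.95² + 8.06²) / 7.5² = 17.88, rounded up to 18. Then 18 / 0.9 = 20. The stated 18 and 20 reproduce, so this point does not rest on a sample-size error.

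**4. How the order could reach the result.** The Analysis section plans a repeated-measures analysis of variance with Bonferroni comparisons within and between groups.

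- *Pre-test answered with the arm known.* With two time points, the group-by-time effect is (post − pre) in one arm minus (post − pre) in the other. A shift of s points in one arm's pre-test alone moves this estimate by s points.
- *Refusal linked to the arm.* If a fraction r of one arm refuses, and refusers differ from those who stay by d points, the mean of those who stay differs from the full arm's mean by r × d. The documents give neither r nor d. Assumed ranges are r = 0.10 to 0.30 and d = 4 to 8.

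| r | d = 4 | d = 8 |
|---|---|---|
| 0.10 | 0.4 (5% of 7.5) | 0.8 (11%) |
| 0.20 | 0.8 (11%) | 1.6 (21%) |
| 0.30 | 1.2 (16%) | 2.4 (32%) |

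The refusal shift applies to a comparison of arm means at one time. If refusers would have differed equally at both times, it cancels in the comparison of changes.

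**The case against.** The strongest reply is that the narrative is loosely written. The explanation is placed before participation in the research, and the format choice is offered to participants in general. Only after consent and pre-test does the text say that women allocated to the intervention are invited to their sessions, which would fit disclosure of the arm after baseline. The flow diagram is not available in the text reviewed, so its order cannot be checked. The article also says that the researcher will be unaware of the groups, and it places eligibility before invitation.

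Part of this stands. Later disclosure is possible, and the eligibility wording means that exclusion after allocation cannot be asserted. But the stated order of assignment, consent and pre-test remains. A statement about the researcher neither changes that order nor blinds the woman, who is the one giving consent and answering the questionnaire.

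Four stronger readings are tempting and are not supported:

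- **A large loss of women and power through failed PCL-5 screening.** A reader might apply the PTSD rates in the Introduction (61.6% and almost 92%) to the 40 women. Those rates come from Tehran and from another area, not Isfahan, and the invited women are described as already eligible.
- **The teaching student makes the calls and so knows the arm at consent.** The article names no caller. It names the student only as instructor.
- **Women had already been allocated without consent.** Trial status says "To date, 40 participants have been randomly selected", while Randomization and data management says that "recruitment will begin in April 2024, and will end in January 2025". Selection need not mean allocation, and a conflict about dates says nothing about the order of consent.
- **Permuted blocks are required.** That is a design preference and does not bear on the order of steps.

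**Conclusion.** The point holds as a fault in the stated sequence. The implementation section puts assignment before consent and pre-test, the data collection section agrees, and nothing in the article says otherwise. A team following the text would leave refusals and the self-reported baseline open to influence from the arm.

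How much bias would follow cannot be derived from the documents. It requires that the arm is known or guessed when consent is sought or the pre-test is completed. Different programmes, a format choice before consent and no described concealment make that plausible, but do not prove it. The illustrative shift of 0.4 to 2.4 points depends wholly on the assumed refusal fractions and score differences. Exclusion for ineligibility after allocation is a possibility left open by the text, not something the text shows.

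**What to change.** Reword Randomization and data management, the implementation section and Data collection tools and methods so that all three give one order:

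1. telephone invitation and explanation;
2. written consent;
3. confirmation of eligibility, including the PCL-5 and the psychologist's assessment;
4. statement of preference for group or individual sessions, asked of every woman;
5. the full pre-test;
6. allocation, then disclosure of the arm.

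State that the allocation list is kept from those who recruit and those who teach. If any woman was allocated before she consented, report her in the participant flow by arm, with the reason if she did not continue.

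The change reorders steps that the plan already contains. Its cost is that some women will be screened and complete the pre-test without being randomised.
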